## Abstract

**Background:**

Magnetic resonance image–guided high-intensity–focused ultrasound (MR-HIFU) is a rather new, noninvasive option for the treatment of uterine fibroids. It is safe, effective, and has a very short recovery time. However, a lack of prospectively collected data on long-term (cost-)effectiveness of the MR-HIFU treatment compared with standard uterine fibroid care prevents the MR-HIFU treatment from being reimbursed for this indication. Therefore, at this point, when conservative treatment for uterine fibroid symptoms has failed or is not accepted by patients, standard care includes the more invasive treatments hysterectomy, myomectomy, and uterine artery embolization (UAE). Primary outcomes of currently available data on MR-HIFU treatment often consist of technical outcomes, instead of patient-centered outcomes such as quality of life (QoL), and do not include the use of the latest equipment or most up-to-date treatment strategies. Moreover, data on cost-effectiveness are rare and seldom include data on a societal level such as productivity loss or use of painkillers. Because of the lack of reimbursement, broad clinical implementation has not taken place, nor is the proper role of MR-HIFU in uterine fibroid care sufficiently clear.

**Objective:**

The objective of our study is to determine the long-term (cost-)effectiveness of MR-HIFU compared with standard (minimally) invasive fibroid treatments.

**Methods:**

The MYCHOICE study is a national, multicenter, open randomized controlled trial with randomization in a 2:1 ratio to MR-HIFU or standard care including hysterectomy, myomectomy, and UAE. The sample size is 240 patients in total. Women are included when they are 18 years or older, in premenopausal stage, diagnosed with symptomatic uterine fibroids, conservative treatment has failed or is not accepted, and eligible for MR-HIFU. Primary outcomes of the study are QoL 24 months after treatment and costs of treatment including direct health care costs, loss of productivity, and patient costs.

**Results:**

Inclusion for the MYCHOICE study started in November 2020 and enrollment will continue until 2024. Data collection is expected to be completed in 2026.

**Conclusions:**

By collecting data on the long-term (cost-)effectiveness of the MR-HIFU treatment in comparison to current standard fibroid care, we provide currently unavailable evidence about the proper place of MR-HIFU in the fibroid treatment spectrum. This will also facilitate reimbursement and inclusion of MR-HIFU in (inter)national uterine fibroid care guidelines.

**Trial Registration:**

Netherlands Trial Register NL8863; https://www.trialregister.nl/trial/8863

**International Registered Report Identifier (IRRID):**

DERR1-10.2196/29467

## Introduction

Fibroids are the most common benign gynecological tumors in women of reproductive age, occurring in up to 70% of the population. Approximately 25% of the uterine fibroids are symptomatic [1]. Symptoms include abdominal pain, menstrual disorders, lower urinary tract or bowel symptoms, and fertility disorders [2]. On a global level, fibroids represent an enormous economic burden to the health care system and costs can reach as much as US $5.9-34.4 billion each year in the United States [3]. Conservative treatment of fibroids fails in 50% of patients, many of whom subsequently opt for surgical procedures [4]. Hysterectomy is currently the most common treatment for symptomatic uterine fibroids, with millions of procedures performed annually around the world [5]. However, hysterectomies and myomectomies have a high risk of complications, long recovery, and might compromise future pregnancies [6], with the latter mainly due to peritoneal and intrauterine adhesions, a high rate of abnormal placentation, and fragility of myometrium as a result of myomectomy [7]. Furthermore, even a hysterectomy does not guarantee an intervention-free life, mostly because of complications caused by the operation itself [8]. This has led to a strong desire for less invasive treatments [4].

Currently, uterine artery embolization (UAE) is the only reimbursed minimally invasive treatment available in the Netherlands. The general treatment results after UAE are 60% fibroid volume reduction and on average 80%-90% patient satisfaction [9]. Complications after UAE include nontarget embolization, infection/septicemia and ovarian failure due to impairment of ovarian blood flow, and infection leading to fallopian tube damage with subsequent infertility [9,10].

Magnetic resonance image–guided high-intensity–focused ultrasound (MR-HIFU) is a thermal ablation technique, which enables noninvasive treatment of symptomatic uterine fibroids by selective tissue heating [11]. The ultrasound transducer produces convergent high-intensity ultrasound waves. The targeted tissue absorbs the acoustic energy leading to a temperature rise, which causes coagulative necrosis [12]. Magnetic resonance imaging (MRI) facilitates treatment planning and real-time monitoring by temperature mapping [13]. Directly after MR-HIFU, a contrast-enhanced MRI scan can visualize the ablated tissue, referred to as the nonperfused volume (NPV). NPV% (NPV divided by the initial fibroid volume) is one of the commonly used parameters to indicate technical treatment success [11].

When the MR-HIFU therapy of uterine fibroids was first introduced in clinical practice, it was allowed to ablate only 33%, and later on 50%, of the uterine fibroid. However, it soon became clear that clinical outcomes are closely related to high NPV percentages. Therefore, nowadays full ablation protocols are used [12,14]. In addition, better results and less adverse events were seen when using the latest generation of treatment devices [11]. Not all patients with symptomatic uterine fibroid are eligible for MR-HIFU treatment due to either patient or fibroid tissue characteristics, such as the number of fibroids or the extent of vascularization of a fibroid and the possibility to heat the tissue [15]. A wish to conceive is not a contraindication, although data on pregnancy outcomes remain sparse [16,17]. Careful screening is in all cases recommended [18]. Hitherto, only 5 studies were published on the cost-effectiveness of the MR-HIFU uterine fibroid treatment [19-23]. All used outdated, less effective MR-HIFU treatment protocols and costs of sanitary products, over-the-counter remedies, and alternative and complementary therapies were typically not taken into account. Nevertheless, these cost-effectiveness studies still concluded that MR-HIFU can be cost-effective at commonly accepted willingness-to-pay thresholds [11].

## Methods

This protocol was developed according to the Standard Protocol Items: Recommendations for Interventional Trials (SPIRIT) 2013 statement [28].

### Study Design and Setting

The MYCHOICE study (MYoma treatment Comparison study: High-intensity image–guided fOcused ultrasound versus standard [minimally] Invasive fibroid care—a (Cost-)Effectiveness analysis; Netherlands Trial Register NL8863) is designed as an open, national, multicenter, RCT. By including both academic and nonacademic centers as participating hospitals in the MYCHOICE study, high volume and expertise are warranted. Participating hospitals provide a representative geographic spread across the country. All participating hospitals are specialized uterine fibroid centers and perform standard (minimally) invasive fibroid care. The MR-HIFU treatment will, however, be performed in the only 2 hospitals in the Netherlands that offer MR-HIFU treatment (Isala Zwolle and University Medical Center Utrecht) in addition to standard uterine fibroid care.

### Study Population and Eligibility

#### Overview

Our study population consists of women in the premenopausal phase visiting the gynecological outpatient clinic with symptoms caused by uterine fibroids. Symptoms of fibroids may comprise heavy menstrual bleeding and bulk symptoms such as pelvic pressure, micturition/defecation problems, or pain symptoms. A combination of several symptoms or a single symptom will be equally qualified as “symptomatic.” To optimize external validity of our study results, the inclusion and exclusion criteria defined in this study (Textbox 1) are similar to the inclusion and exclusion criteria applied for MR-HIFU in clinical practice. However, 2 exceptions are made. Women need to be motivated to undergo 1 of the 3 treatments in the control group, in case of being randomized to the control group, before participating in the MYCHOICE study. Furthermore, a wish to conceive within 1 year after inclusion is a reason to be not eligible for participating, because there is not yet a consensus about the standard of care for these women. Women without an active child wish but for whom a pregnancy in the future is not ruled out can be included in the study.

The MYCHOICE study procedure consists of several steps (Figure 1).

The eligibility procedure for this study consists of 2 screening phases. Only women that are considered eligible for participating in the study based on these 2 screening phases will be randomized.

Inclusion criteria for participation in the MYCHOICE (MYoma treatment Comparison study: High-intensity image–guided fOcused ultrasound versus standard [minimally] Invasive fibroid care—a [Cost] Effectiveness analysis) study.
**Inclusion criteria**
Symptomatic fibroids warranting (minimally) invasive treatment, that is, either hysterectomy, myomectomy, or uterine artery embolizationConservative treatment failed or not acceptedPremenopausalAge ≥18 yearsEligible for magnetic resonance image–guided high-intensity focused ultrasound (MR-HIFU) treatment.
**Exclusion criteria**
Asymptomatic fibroidsPostmenopausalBMI of ≥35 kg/m^2^ or abdominal subcutis ≥4 cm or bothMore than 5 uterine fibroids unless 1 or 2 fibroids causing the symptoms can be clearly identifiedMagnetic resonance imaging contraindications or contrast allergyCurrent pregnancyA wish to conceive within 1 year after inclusionSuspicion of malignancyDominant adenomyosis, defined as more volume of adenomyosis rather than fibroidsNot willing to accept pretreatment with leuprorelin before MR-HIFU in case of a uterine fibroid with a diameter >10 cm or classified as Funaki 3Not willing to remove an interfering intrauterine contraception device prior to MR-HIFUNot eligible for MR-HIFU as determined by the multidisciplinary MR-HIFU team in Isala based on a screening magnetic resonance imaging:Uterine fibroid(s) either submucosal or subserosal stalked or with a diameter <2 cmFibroids suitable for hysteroscopical removalDistance of abdominal wall to the dorsal side of uterine fibroids expected to be >12 cm even after the use of manipulation techniquesCalcified uterine fibroids or fibroids without contrast enhancement

**Figure 1 figure1:**
[figure not shown]
Flow diagram of the MYCHOICE procedure. MR-HIFU: magnetic resonance image–guided high-intensity focused ultrasound; MRI: magnetic resonance imaging; MYCHOICE: MYoma treatment Comparison study: High-intensity image–guided fOcused ultrasound versus standard (minimally) Invasive fibroid care—a (Cost-)Effectiveness analysis.

#### Phase 1 of the Screening Procedure

Patients presenting with uterine fibroid–related symptoms at the Department of Gynecology of the participating centers will undergo standard consultation, physical examination, and vaginal ultrasonography. The patient is briefly informed about the study when she appears to be eligible for participation in the study based on the physical examination and the vaginal ultrasonography (step 1 in Figure 1). In case the patient is interested in participating in the study, an appointment with a member of the research team or local research nurse will be made and the patient will receive more detailed study information to read at home (step 2 in Figure 1). In case a patient does not want to participate, the gynecologist asks the patient if she is willing to disclose the reason for not participating. During the appointment with a member of the research team or local research nurse, additional counseling will take place.

#### Phase 2 of the Screening Procedure

Once the patient has signed the informed consent form, a screening MRI scan according to a predefined protocol will be planned in the local hospital (step 3 in Figure 1).

Final eligibility of the patients of all participating centers will be determined by the multidisciplinary MR-HIFU team in the coordinating center based on the screening MRI scan and the inclusion and exclusion criteria (step 4 in Figure 1). These meetings will be accessible to members of the other participating hospitals. By performing central screening, a bias caused by differences per site is minimized and eligibility for MR-HIFU is secured.

### Intervention

#### Pretreatment

The participant’s gynecologist and general practitioner are informed about the outcome of the eligibility assessment and, if the patient is considered eligible, the randomization outcome (step 5 in Figure 1). Subsequently, the gynecologist will inform the patient about the outcome and baseline data will be collected by a member of the research team or the local research nurse and entered into the electronic case report form (Research Manager). In case a patient is randomized to the MR-HIFU treatment arm, she will be referred to an MR-HIFU performing hospital if her hospital is not 1 of the 2 hospitals in which the MR-HIFU treatment is performed. In case she is randomized to the standard care treatment arm, she can be treated in her own hospital.

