### Data Collection

Data collection will take place before treatment, and at 3, 6, 12, and 24 months after treatment by questionnaires. Furthermore, baseline data of patient and treatment costs will be collected before treatment and after data lock-in (Table 1).

**Table 1 table1:** Timeline of data collection.

Data	Baseline	Treatment	3 months	6 months	12 months	24 months	Data lock-in
Informed consent	X						
Patient characteristics^a^	X						
Pregnancy outcomes^b^	X					X	
UFS-QoL^b,c^	X		X	X	X	X	
EQ-5D-5L^b,d^	X		X	X	X	X	
Onset of menopause^b^						X	
(Time to) reintervention^a^			X	X	X	X	X
Adverse events/complications^a^		X	X	X	X	X	
PREM^b,e^	X		X	X	X	X	
Recovery time^a^		X	X	X			
Medical Consumption Questionnaire^b,f^	X		X	X	X	X	
Productivity Costs Questionnaire^b,f^	X		X	X	X	X	
Costs of treatment^a^							X
Reason for not participating^a,g^	X						

^a^Retrieved from questionnaires and medical record.

^b^Retrieved from questionnaires solely.

^c^UFS-QoL: Uterine Fibroid Symptom and Quality of Life questionnaire.

^d^EQ-5D-5L: 5-level version of the EuroQoL Questionnaire.

^e^PREM: patient-reported experience measurement

^f^Used for the cost-effectiveness analysis.

^g^Data collected by the gynecologist in case of not willing to participate.

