The unit costs of direct medical out-of-hospital costs, direct nonmedical costs, and indirect costs will also be based on Dutch guidelines for cost calculations in health care. The following altered patient questionnaires will be used: iMTA Productivity Cost Questionnaire (iPCQ) and iMTA Medical Consumption Questionnaire (iMCQ). The iPCQ questionnaire is a short generic measurement instrument on the impact of disease on the ability of a person to perform work. It also contains questions about absence from unpaid labor. This questionnaire is a generic instrument for measuring medical costs, including questions related to frequently occurring contacts with health care providers. All questionnaires will be sent by email or post according to the preference of the participant at baseline and at 3, 6, 12, and 24 months after treatment (Table 1). Patients will receive an automatic reminder by email. Indirect costs due to absence from work will be estimated as the actual working time lost (hours) multiplied by the average net income according to the friction cost method.

A decision analytic model with lifetime horizon will be developed by combining costs and effects. Complete uncertainty analyses (deterministic and probabilistic sensitivity analyses) will be performed.

In addition, a budget impact model will be constructed, taking the (gradual) implementation of MR-HIFU over time, the initial investments, and the savings into account that were shown to be realistic in the trial. The model will use different perspectives: (1) The net Dutch Budgetary Framework for Healthcare (Budgettair Kader Zorg) perspective; and (2) health insurance/third-party payer perspective.

The budget impact model is performed through modeling and analyzed in a probabilistic way.

Because MR-HIFU is an outpatient treatment with a fast(er) recovery, it is expected to be cheaper than the current standard (minimally) invasive treatments, especially from a societal perspective.

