Patient-reported satisfaction with treatment and treatment preference (PREM^f^)	Because a randomized controlled trial will be performed, satisfaction with treatment might be affected by not being allocated to preferred treatment. Furthermore, we expect women declining participation because of the randomization aspect of the trial.	The PREM consists of a concise set of statements about the experience of the patients with the treatment and whether they would recommend the treatment to a friend. In addition, the preference will be registered for a particular treatment of potential participants before randomization. Women who decline participation in the study will also be asked if they are willing to disclose their reasons for declining.	The PREM score is scored on a 5-point Likert scale: higher score represents better experience. Whether there is a difference in PREM outcome between the 2 treatment arms is determined by linear regression analysis.
(Co)medication	Women (still) experiencing symptoms after treatment may take or may start to take medication to relieve these symptoms. Medication might also be used as contraceptive and to mask possible fibroid-related symptoms at the same time.	Data on any prescribed or over-the-counter medication taken to reduce fibroid symptoms as reported by the patient will be collected via the questionnaires at baseline, 3, 6, 12, and 24 months after treatment.	The number of women taking medication to suppress fibroid-related symptoms is measured at baseline and 3, 6, 12, and 24 months after treatment. The absolute numbers and percentage of women taking comedication per group per time point will be presented.
Reintervention rate and time to reintervention	A reintervention is defined as an additional intervention due to persisting or recurring symptoms of the treated fibroid or due to complications of the initial fibroid treatment.	Occurrence and type of reintervention are collected via both electronic patient file and questionnaires at 3-, 6-, 12-, and 24-month follow-up.	The reintervention rate at the follow-up time point of 24 months after MR-HIFU^g^ is presented as percentage reinterventions with its 95% CI. Reintervention rate will be presented per treatment arm but also per treatment. To investigate whether the time to reintervention differs between the 2 treatment arms, Cox proportional hazards analysis will be used.

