### Sample Size

The MYCHOICE study is a noninferiority trial for which we hypothesize that MR-HIFU is noninferior to the group of standard (minimally) invasive treatments, accepted by a ≤15 points difference in symptom reduction at 24 months’ follow-up as determined with the SSS (range 0-100 points) part of the UFS-QoL questionnaire. We expect that women participating in this trial have a slight preference for the noninvasive MR-HIFU treatment. We therefore choose to use an unbalanced design in which participants are allocated to the intervention or usual care group at a 2:1 ratio, resulting in a larger sample size in the MR-HIFU treatment group. With a larger sample size of the MR-HIFU treatment group, we will be able to gather more data on this new treatment while the effectiveness of standard care is already much better documented. Randomization, stratified by center, will be performed using a computer-generated randomization system, which randomly selects block sizes of 3, 6, or 9. Previous studies concerning (minimally) invasive treatments were performed with women with an average baseline UFS-QoL SSS of 55-65 points [33]. Treatment initiated a decrease of 30-47 points on SSS 12 months after these combined treatments. Hitherto, there are 2 MR-HIFU studies published that used a full ablation protocol, had the same 12-month follow-up period as the studies on (minimally) invasive treatments, and in which women participated with a baseline UFS-QoL SSS of 55-65 points. These women showed an SSS reduction of 30-40 points at follow-up [34,35]. In our study population we expect comparable baseline SSS in the MR-HIFU and standard care group. However, because hysterectomy results in a somewhat higher SSS reduction than the uterus-saving treatments, we assume in our power calculation an a priori 5-point delta between both the MR-HIFU and standard care group in favor of the standard care group. Using a noninferiority margin of 15 points with α (1-sided)=0.025, β=.1, and an SD of 20 points, we estimate that 192 participants (128 patients in the MR-HIFU treatment group and 64 patients in the [minimally] invasive treatment group) will be required to test noninferiority of MR-HIFU. Anticipating a 20% loss to follow-up, we need to include 160 patients in the MR-HIFU group and 80 patients in the (minimally) invasive treatment group. The noninferiority margin and the SD of 20 points were determined in consultation with the Dutch Society for Obstetrics and Gynecology and were similar to the noninferiority margin used in the MYOMEX-2 study [36].

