### Statistical Methods

In this study, data will initially be analyzed on an intention-to-treat-basis (including treatment failures) but a per-protocol analysis will also be performed. QoL at the follow-up time point of 24 months after treatment is determined as a change in SSS between baseline and 24 months’ follow-up. The difference between the symptom reduction after MR-HIFU and standard (minimally) invasive fibroid care including 97.5% CI is determined using linear regression analysis with a correction for baseline SSS. Although symptom reduction 24 months after MR-HIFU will be expected to be noninferior to standard (minimally) invasive fibroid care, the time course of symptom reduction may differ between the 2 treatment arms. This will be investigated with longitudinal covariance analysis. A faster symptom reduction in the usual care arm may be caused by a faster symptom reduction after hysterectomy. Therefore, a subgroup analysis in which the individual treatments are compared will be performed.

Patients can leave the study at any time for any reason if they wish to do so, without any consequences. In case they decide to withdraw before treatment or within the first 3-month follow-up, they will be included in the database, but an additional patient will be included to achieve the required sample size and reach primary outcome. In case patients withdraw after the 3-month follow-up, they are considered nonresponders. As much precautions as possible will be taken to prevent missing data. However, missing values are expected to occur in our trial due to technical failures and loss to follow-up. In case missing data reach 5%, additional analyzes will be performed to identify a plausible assumption, that is, missing not at random, missing at random, or missing completely at random. Subsequently, an analysis method that is valid under that assumption will be used.

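### The baseline symptom score is not placed before randomization, and the stated order of steps allows it to be taken once the woman knows her arm

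*Protocol article*

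**What the plan says.** Protocol article, Pretreatment: the gynecologist and general practitioner receive the eligibility result and, "if the patient is considered eligible, the randomization outcome (step 5 in Figure 1"). The next sentence reads: "Subsequently, the gynecologist will inform the patient about the outcome and baseline data will be collected by a member of the research team". A nurse at the local site may do this instead, and the data go into the electronic case report form.

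Data Collection: "Data collection will take place before treatment, and at 3, 6, 12, and 24 months after treatment by questionnaires". Table 1 marks the UFS-QoL, the EQ-5D-5L and the two cost questionnaires under Baseline, and its footnotes give questionnaires as their only source. Under Primary Outcomes, "All questionnaires will be sent by email or post according to the preference of the participant at baseline" and at the follow-up times.

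Study Design and Setting: the study "is designed as an open, national, multicenter, RCT". Sample Size: "We expect that women participating in this trial have a slight preference for the noninvasive MR-HIFU treatment".

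Statistical Methods: the primary outcome "is determined as a change in SSS between baseline and 24 months" of follow-up, and the arms are compared by linear regression corrected for baseline SSS.

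Only one patient-reported item is explicitly timed ahead of allocation. In the patient-satisfaction row of Table 2, "the preference will be registered for a particular treatment of potential participants before randomization".

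**The concern.** The two sentences under Pretreatment put randomization first, then list telling the patient and collecting baseline data together. If the UFS-QoL belongs to those baseline data, the SSS that starts the primary endpoint is a post-randomization measurement, reported by a woman who may already know her arm.

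The article itself gives reasons why reporting might then differ by arm. It expects a preference for MR-HIFU. It says in Table 2 that satisfaction may suffer when a woman does not get the treatment she prefers. It says under Recruitment that the trial is the only route to MR-HIFU in the country.

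A covariate that is itself affected by allocation cannot correct for that effect. The baseline EQ-5D-5L, which feeds the quality-adjusted life years, and the baseline cost questionnaires follow the same schedule.

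**Working it through.** **1. The plan's own figure.** Inputs from Sample Size: margin 15, SD 20, assumed true difference 5 in favor of standard care, one-sided alpha 0.025, power 90%, ratio 2:1.

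- Control arm: (1 + 1/2) × (1.960 + 1.282)² × 20² / (15 − 5)² = 63.04, rounded up to 64. MR-HIFU arm: 2 × 64 = 128. Total 192.
- With 20% loss: 64/0.8 = 80 and 128/0.8 = 160. Total 240.
- SE = 20 × √(1/128 + 1/64) = 3.062. Power = Φ(10/3.062 − 1.960) = 90.4%.

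The stated sample size is reproduced exactly and is not in question.

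**2. What the text fixes about timing.**

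| Section | What it ties baseline to |
|---|---|
| Pretreatment | after the randomization outcome is issued, alongside telling the patient |
| Data Collection | before treatment |
| Table 1 | a Baseline column with no position relative to randomization |
| Table 2, satisfaction row | preference only: before randomization |

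No section shown places the UFS-QoL or EQ-5D-5L before randomization.

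**3. How a shift reaches the result.** Let s be the difference between arms in reported baseline SSS that is caused by knowing the allocation. Let b be the within-arm slope of 24-month SSS on baseline SSS. The adjusted difference in 24-month SSS is the raw difference minus b times the difference in baseline means, so a false baseline difference s biases it by b × s. An unadjusted change score would be biased by the full s. A simulation with 128 and 64 women, correlation 0.5, no true effect and control baselines raised by 5 points gave −2.5 points after adjustment and −5.0 points for raw change, both against MR-HIFU.

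**4. Size.** The documents give neither s nor b. Assumed ranges: s = 2 to 5 points, b = 0.3 to 0.7, with the SE held at 3.062.

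- Bias against MR-HIFU: power = Φ((10 − bs)/3.062 − 1.960).
- Bias in favor of MR-HIFU: one-sided error at the margin = Φ(bs/3.062 − 1.960).

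| s | b | Bias | Power if against MR-HIFU | Error at margin if in favor |
|---|---|---|---|---|
| 0 | – | 0 | 90.4% | 2.5% |
| 2 | 0.3 | 0.6 | 86.7% | 3.9% |
| 2 | 0.5 | 1.0 | 83.6% | 5.1% |
| 3 | 0.5 | 1.5 | 79.3% | 7.1% |
| 5 | 0.5 | 2.5 | 68.8% | 12.6% |
| 5 | 0.7 | 3.5 | 56.5% | 20.7% |

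**5. Direction.** A control woman disappointed by her allocation may report a worse, that is higher, baseline SSS. Her later reduction then looks larger, and MR-HIFU looks worse by comparison. A woman relieved to get MR-HIFU who reports a milder baseline has the same effect. The preference that the article expects therefore points to the power column. The error column needs the reverse shift, for which the article suggests no mechanism.

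**The case against.** The sentence under Pretreatment speaks of baseline data without naming a questionnaire. It describes staff collecting data and entering them in the case report form, while the UFS-QoL comes from questionnaires sent by email or post. It joins disclosure and collection with a plain conjunction, so the order of those two acts is not strict. The Baseline column of Table 1 also holds informed consent and reasons for not participating, which must come before randomization, so the column does not mark a single post-allocation visit. Figure 1, which carries the step sequence, is not shown, and the full protocol may settle the matter.

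All of this stands. A reader might infer that the UFS-QoL is definitely completed after disclosure; the text does not establish that. A reader might also infer that the main danger is a false claim of noninferiority. The stated preference does not support this, because it points the other way. Nor do the documents support any single size of shift: they call the preference slight, and a 5-point shift would equal the whole treatment difference assumed in the power calculation.

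What does not go away is that the article sets randomization ahead of baseline collection, gives baseline no anchor other than treatment, and shows elsewhere that it can specify a time before randomization when it means one. A site following this text could take the baseline SSS after disclosure and still comply.

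**Conclusion.** The concern holds as a timing rule that leaves the baseline SSS open to influence from the allocation, not as proof that it has been influenced. Under the assumed ranges the bias in the adjusted difference is 0.6 to 3.5 points, against the 10 points between the assumed difference and the margin. The likelier direction costs power: 86.7% down to 56.5%, instead of 90.4%. The opposite direction would raise one-sided error to between 3.9% and 20.7%, instead of 2.5%. These figures rest on assumed values for shift and slope and on the planned SD of 20. Correcting for baseline SSS shrinks the distortion but cannot eliminate it. The point deserves action because the same value serves as start of the endpoint and as covariate, and because a baseline taken after disclosure cannot be replaced later.

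**What to change.** - State that the baseline UFS-QoL, EQ-5D-5L, iMCQ and iPCQ are completed after consent and before randomization, or at the latest before the allocation is released to the gynecologist and the patient. Consent already precedes the screening MRI and randomization, so the interval exists.
- Correct the order under Pretreatment and the time anchor under Data Collection to match. If sites already work this way, correcting the text is all that is needed.
- For women already enrolled, record whether the baseline questionnaire was completed before or after disclosure, and compare baseline SSS between arms within each of those groups.
- Add a sensitivity analysis that compares 24-month SSS between arms without using a post-disclosure baseline as start value or covariate. Do not exclude the women concerned: if the stated order was followed, that could remove nearly everyone enrolled so far.

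Cost: one procedural rule and two text corrections. The sample size stays at 192 evaluable and 240 enrolled. Some women who fail MRI screening will complete a questionnaire that is not used. The sensitivity analysis is less precise than the adjusted one: with equal SDs and a baseline correlation of 0.5 (an assumption), its variance is 1/(1 − 0.5²) = 1.33 times as large.
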